#### Visit 12 (last day of hospitalization)

Physical examination and laboratory analyses (AST, ALT, GGT, alkaline phosphatase, bilirubin, factor V, INR, platelets, creatinine, GFR, lactates) will be performed. Immunosuppression medication will be confirmed and post-transplant complications (Clavien–Dindo Score, CCI) will be assessed. Concomitant medications and adverse events will be collected. Post-transplant ICU and hospital stay will be assessed.

#### Visit 13 (3 months (± 30 days))

After liver transplantation, patients have regular checks at hospital, where physical examinations and lab test are performed (AST, ALT, GGT, alkaline phosphatase, bilirubin, factor V, INR, platelets, creatinine, GFR). During this appointment, the following will be recorded: the incidence of main postoperative complications (kidney function disorders, need for dialysis, infections, cholestasis and biliary obstructions, vascular complications, acute rejection, arterial or portal vein thrombosis, biliary fistula), Clavien–Dindo classification score, comprehensive complication index (CCI), reintervention, length of stay in intensive care unit, length of hospital stay, retransplantation, or death within 3 months after liver transplantation.

Adverse events and concomitant medications will be collected.

#### Visit 14–15 (6 months and 9 months after transplantation (± 30 days))

After liver transplantation, patients have regular checks at hospital, where physical examinations and lab tests are performed (AST, ALT, GGT, alkaline phosphatase, bilirubin, factor V, INR, platelets, creatinine, GFR). During this appointment, further examinations, modification of common medications, adverse events, or post-transplant complications will be noted and treated according to the routine management of patients after liver transplantation if necessary. Results of the checks will be documented in the eCRF.

Adverse events and concomitant medications will be collected.

#### Visit 16 (12 months after transplantation, outpatient control, final study visit closure, (± 30 days)

This is the last study visit. Patients will have physical examinations and lab tests (AST, ALT, GGT, alkaline phosphatase, bilirubin, factor V, INR, platelets, creatinine, GFR). During this appointment, further examinations, modification of concomitant medications, adverse events, or post-transplant complications will be noted and treated according to the routine management of patients after liver transplantation if necessary. Results of these checks will be documented in the eCRF. This is also the final control, including study closure and liver contrast enhanced MRI/MRCP.

Serious and adverse events will be evaluated throughout study participation.

### Sample size {14}

A sample size of 119 patients per randomized group (238 in total) is needed based on the following parameters:Expected decrease of EAD rate from 30% in the control group to 15% in the HOPE group (50% decrease of EAD based on previous preliminary clinical studies) [15, 20]Alpha: 0.05Power: 0.80Two-sided test

The sample size was calculated using the “pwr.2p.test” function of R (R Foundation for Statistical Computing, Vienna, Austria), package “Pwr”. In order to take into account a 10% proportion of dropouts or patients who prematurely terminate the study, 133 patients shall be recruited per group, i.e., 266 patients in total. Because there is about 20% of dropouts on the waiting list in France (2017 annual report of the “Agence de la Biomédecine”), and about 50% of liver grafts are provided from ECD, it is expected that 660 patients should be included in the study to be able to randomize 266 patients. In order not to slow down randomizations as they approach the total needed, inclusions will be possible beyond 660 patients within the limit of 1000 patients included.

According to EUROTRANSPLANT and the “Agence de la Biomédecine”, 50% of liver grafts are provided from ECD with the rate increasing over recent years. To be on the safe side, we expect that centers may randomize half of their potential transplanted patients with ECD, namely 25% of their total number of liver transplantations a year.

### Recruitment {15}

The 24-month inclusion period allows a reasonable mean rate of randomized patients of 1.39 patient/month/center. All participating centers are large and well-experienced liver transplantation centers in France. To ensure an adequate number of patients will be enrolled in the required time frame, the participating centers will be asked to report on a regular basis their problems related to enrolment, in order to find adequate responses to improve the enrolment rate. Moreover, to stimulate enrolment, a newsletter describing the enrolment status will be sent regularly to all centers.

## Assignment of interventions: allocation

### Sequence generation {16a}

Randomization will be performed after the allocation of the graft or after the harvesting team has macroscopically assessed the graft, according to the center practice.

It will be stratified by center and MELD score at the time of transplantation, with a cut-off of 30 (MELD < 30 versus MELD ≥ 30).

The randomization process will be centralized and carried out via Ennov Clinical software. The randomization list will be drawn up by the methodologist/biostatistician of the Clinical Research Center at the Croix-Rousse University hospital, Lyon, France.

The randomization list will be kept for 25 years in a tamper-proof envelope with the mandatory information (signature of the person in charge of the list, date and version number, complete title, and code of the research protocol). This list will also be sent to the Clinical Research Center data manager for implementation in the Ennov Clinical software.

The investigator or a person designated by the principal investigator will randomize patients via the Ennov Clinical software. Only authorized persons will be able to perform the randomization. A confirmation email will be sent to the person who performed the randomization after each randomization, to the investigator associated with the patient, and to the management center.

In case of cancellation of the transplant for any reasons, the data manager will cancel the randomization. The patient will remain included in the study for randomization in one of the study arms.

The whole process (randomization, modifications, etc.) will be recorded in the audit trail of the study, which will be integrated in the clinical data management system (CDMS). This audit trail will be transmitted at the end of the study to be archived with all the study documents.

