#### Conduct of the study

The overall schedule and time commitment for trial participants are summarized in Table 1.

**Table 1 Tab1:** Schedule of enrolment, interventions, and assessments in the HOPExt trial

Stages	V1 screening	V2 inclusion		V3	V4	V5–V11	V12	V13–V16
Time point	At inscription for LT or at pre-LT visit	D0 At hospitalization for LT	D0 HOPE group only	D0 + 6h (+/-2h) after LT	D0 + 12h (+/-2h) after LT	Day 1 to day 7 (+/-1day)	End of hospital stay	M3; M6: M9 and M12 (+/-30 days)
Actions								
Inclusion/non-inclusion criteria	X	X						
Informed consent	X							
Medical history and patient characteristics^1^	X							
MELD score	X At inscription	X						
Randomization^2^		X						
Clinical examination^3^		X					X	X
Biological analyses^4^		X (before LT)		X	X	X	X	X
Child–Pugh score		X (before LT)						
Donor characteristics^5^		X						
HOPE perfusion parameters^6^			X					
Bacteriological and fungal analyses^7^		X	X					
Intra-operative data^8^		X						
Liver biopsy^9^		X both groups	X					
Machine perfusate sample^10^			X					
ICU and hospital stay							X	
Morbidity (Clavien–Dindo score, CCI)							X	X At M3 only
Concomitant medication		X		X	X	X	X	X
Adverse events		X		X	X	X	X	X
Abdominal contrast enhanced MRI/MRCP								X At M12 only

^1^Patient characteristics: age, gender, height, weight, BMI, blood group, cause of cirrhosis, indication for transplantation, medical history (diabetes mellitus, arterial hypertension, transjugular intrahepatic portosystemic shunt), pretransplant status of residence (home, hospital ward or intensive care unit (ICU))

^2^Randomization will be performed after the harvesting team has macroscopically assessed the graft and confirmed that the graft will be harvested. After checking the inclusion and non-inclusion criteria, an online randomization tool will be used. Randomization will be stratified by center and MELD score at the time of transplantation with a cut-off of 30

^3^Clinical examination: vital signs (temperature, blood pressure, heart rate), body weight, height, BMI

^4^Biological analyses: AST, ALT, GGT, alkaline phosphatase, bilirubin, factor V, INR, platelets, creatinine, GFR, lactates. At V2 only, a pregnancy test (beta HCG) will be done for women of childbearing age

^5^Donor characteristics**:** age, gender, height, weight, BMI, blood group, length of stay in intensive care unit, cause of death, occurrence of cardiac arrest, biological test (AST, ALT, natremia)

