#### *Inclusion visit/randomization* = *V2*

#####  D0, visit 2

Verification that the consent form was signed by the patient and the investigator.

After the allocation and acceptance of the organs, the investigator will check the eligibility criteria. If the criteria are met, the liver recipient (study participant) will be randomized. The team of local investigators will be informed accordingly in order to set up the perfusion device. If the criteria are not respected, the patient will leave the study (premature termination of participation).

*Randomization*: it is important to note that absolutely no changes will be made to the national liver allocation rules. The study does not interfere or change the process of accepting or declining a liver offered to a certain patient in any way. Once a suitable recipient for the liver is identified, the recipient will be invited to come to the relevant transplant center for the surgical procedure as per routine procedure. Randomization will be performed after the allocation of the graft or after the harvesting team has macroscopically assessed the graft and confirmed that the graft will be harvested, according to the center practice. No study-related factors will be assessed before randomization. After checking the inclusion and non-inclusion criteria, an online randomization tool will be used. Randomization will be stratified by center and MELD score at the time of transplantation with a cut-off of 30.

*Prior to transplantation*: physical examination, vital signs, laboratory values (AST, ALT, GGT, alkaline phosphatase, bilirubin, factor V, INR, platelets, creatinine, GFR, lactates), MELD score (dialysis), CHILD–PUGH score (encephalopathy, ascites, albumin, prothrombin rate), and donor characteristics will be recorded. Concomitant medications and adverse events will be assessed.

*Liver transplantation*: back-table, recipient hepatectomy, and implantation will always be done by the principal investigator and sub-investigators. During recipient hepatectomy, the liver graft will be either stored in cold storage or perfused with the HOPE machine, according to the randomization. Parameters of the HOPE perfusion will be collected. Lot numbers of perfusate (Belzer-MPS) and perfusion device disposables will be recorded in the source document and eCRF.

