## Statistical methods

### Statistical methods for primary and secondary outcomes {20a}

#### Analysis sets

##### Full analysis set (FAS)

All randomized and transplanted subjects will be considered for the FAS analysis (modified intention-to-treat analysis). This population will be used for efficacy analyses.

Patients randomized in the perfusion group (HOPE) and for whom perfusion cannot be initiated for any reason will be analyzed in the intention-to-treat analysis and considered in the group in which they were randomized. This population will be used for efficacy and feasibility analyses.

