##### Safety population (SAF)

This dataset includes all transplanted subjects for whom at least one follow-up safety data is available. This population will be used for safety analyses.

The primary population of interest will be the FAS.

Descriptive summary statistics for continuous variables will include the number of observations (*n*), mean, standard deviation (SD), median, minimum (min), maximum (max), and 25th and 75th percentiles (IQR). Descriptive summary statistics for categorical data will include frequency counts and percentages *N* (%). Percentage calculations will be based on the number of patients for whom there are no missing data.

The primary endpoint will be expressed as the total number of cases in each group and in percentages, with a 95% confidence interval. The categorical variables of the secondary endpoints will also be expressed as the total number of cases in each group and in percentages with a 95% confidence interval.

Categorical variables will be compared between the two study arms using the chi-squared test or the Fisher’s exact test, as appropriate. The continuous variables of the secondary endpoints will be compared using the Mann–Whitney *U* test.

In order to take into account the potential effects of confounders on the primary endpoint, univariate and multivariate logistic regressions will be performed.

90-day morbidity and mortality will be studied using a Kaplan–Meier analysis and comparison between groups will be performed using the log-rank test.

A *p*-value < 0.05 will be considered as statistically significant.

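### Cancelling the randomization whenever the transplant is cancelled removes post-allocation graft losses from every analysis set, and those losses can depend on the arm

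*Protocol article*

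**What the plan says.** Sequence generation {16a} sets the rule: "In case of cancellation of the transplant for any reasons, the data manager will cancel the randomization". It continues: "The patient will remain included in the study for randomization in one of the study arms". No cause is excepted and no time limit is set. The same section adds that "The whole process (randomization, modifications, etc.) will be recorded in the audit trail of the study".

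The analysis sets are defined under Statistical methods {20a}:
- Full analysis set: "All randomized and transplanted subjects will be considered for the FAS analysis (modified intention-to-treat analysis").
- Per-protocol set: a subset of the full analysis set.
- Safety population: "This dataset includes all transplanted subjects for whom at least one follow-up safety data is available".
- One protection is stated: "Patients randomized in the perfusion group (HOPE) and for whom perfusion cannot be initiated for any reason will be analyzed in the intention-to-treat analysis", in the arm to which they were randomized.

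The time of randomization is described in two ways. Table 1, footnote 2, says: "Randomization will be performed after the harvesting team has macroscopically assessed the graft and confirmed that the graft will be harvested". The Inclusion visit/randomization section says: "Randomization will be performed after the allocation of the graft or after the harvesting team has macroscopically assessed the graft and confirmed", according to center practice, and Sequence generation {16a} gives the same two options. The inclusion visit section also has the local team told the result so that the pump can be set up. Who will be blinded {17a} confirms that the trial is open-label.

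**The concern.** Between randomization and implantation, a team that knows the arm prepares the graft, perfuses it if the arm is HOPE, and goes on to implant it. Only HOPE grafts are cannulated and perfused, so only they are exposed to whatever can go wrong in those steps. A marginal graft can also be declined in either arm at this stage. If no transplant follows, the allocation is voided. If the patient later receives another qualifying graft, only the later allocation counts.

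The full analysis set is presented as modified intention-to-treat, but membership depends on an event after randomization that the allocated procedure may influence. The endpoint does not recover these cases: under Outcomes {12}, graft loss counts only within the first 7 postoperative days, so a graft that was never implanted lies outside the definition. If losses before implantation were more frequent under HOPE, the comparison among transplanted patients would favour HOPE, and no analysis set would show it.

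**Working it through.** **1. What each set can contain.** Take a patient randomized to HOPE whose graft is discarded before implantation.
- Full analysis set: requires randomization and transplantation, so the allocation is not counted.
- Per-protocol set: a subset of the full analysis set, so not counted.
- Safety population: transplanted subjects only, so not counted.
- Audit trail: the cancelled randomization is recorded, but the article states no analysis of it.
- Vigilance: serious incidents during organ conservation go to the sponsor, and device-related reactions go to materiovigilance.

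If the graft is transplanted after all, perfused or not, the patient stays in the HOPE arm.

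**2. The plan's own sample size.** Inputs from Sample size {14}: 30% v 15%, two-sided alpha 0.05, power 0.80, 10% dropout. The R package named there uses the arcsine effect size:
- h = 2·asin(√0.30) − 2·asin(√0.15) = 0.3639
- n = 2·((1.960 + 0.842)/h)² = 118.55, rounded up to 119 per group
- 119/0.9 = 132.2, rounded up to 133 per group

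Both stated figures reproduce. There is no arithmetic error.

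**3. Illustration of size.** The protocol gives no cancellation rate, so k = 3 to 5 lost grafts per arm of n = 133 is an assumption. Each loss is counted as a failure in its allocated arm:
- HOPE rate: p2 = (0.15(133 − k) + k)/133
- Control rate: p1 = 0.30 if control has no losses, or (0.30(133 − k) + k)/133 if it has the same number
- Power = Φ{[(p1 − p2)√n − 1.960√(2p̄(1 − p̄))]/√(p1(1 − p1) + p2(1 − p2))}, with p̄ = (p1 + p2)/2

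| Losses | p1 | p2 | Difference (points) | Power |
|---|---|---|---|---|
| none | 30.0% | 15.0% | 15.0 | 84% |
| 3, HOPE only | 30.0% | 16.9% | 13.1 | 71% |
| 5, HOPE only | 30.0% | 18.2% | 11.8 | 62% |
| 3 in each arm | 31.6% | 16.9% | 14.7 | 80% |
| 5 in each arm | 32.6% | 18.2% | 14.4 | 77% |

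For 3 losses in HOPE only: (0.1308 × 11.533 − 1.1745)/0.5921 = 0.565, and Φ(0.565) = 0.714.

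The 84% assumes no dropout. At 119 per group the same formula gives 79.5% with no losses, and 65% to 54% with 3 to 5 losses in HOPE only.

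**4. Effect on a borderline result.** Uncorrected chi-squared test:
- 36/119 v 22/119: p = 0.035.
- Add two HOPE losses as failures, 36/119 v 24/121: difference 0.1042, standard error √(0.25 × 0.75 × (1/119 + 1/121)) = 0.0559, z = 1.86, p = 0.062.
- Add two losses to each arm, 38/121 v 24/121: difference 0.1157, standard error √(0.2562 × 0.7438 × 2/121) = 0.0561, z = 2.06, p = 0.039.

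The balance of losses between the arms matters more than their number.

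**The case against.** The strongest case on the other side has five parts.

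- **Safety events are still reported.** Serious adverse event reporting covers serious incidents during organ conservation. The materiovigilance section covers device-related reactions. The notification-period section sets no time limit for severe effects related to the device or its implementation. A reader might infer that a graft damaged on the pump vanishes from safety altogether; these sections do not support that. What stands is that it enters no safety analysis set.
- **A pump fault does not by itself exclude a patient.** The contraindications and risks section says that a graft remains implantable in cold storage if the machine cannot be run, and the full analysis set keeps such a patient in HOPE. The article mentions no discard for cannulation injury and no rule to discard on microbiology results. The rule bites only when the transplant itself is cancelled.
- **Acceptance of grafts is said to be unaffected.** The protocol states that the study does not alter how livers are accepted or declined, and it places randomization after acceptance. That is a statement of intent. It does not stop a later cancellation by a team that knows the arm, but nothing shows that teams will behave this way.
- **Re-randomization is conditional.** The patient needs another qualifying graft, and Criteria for discontinuing {11b} ends participation for non-transplantable patients.
- **Cancellations unrelated to the arm do not bias the comparison.** Donor and recipient findings can arise in both arms. This is right, but the rule does not separate such reasons from the others.

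Tabulating cancellations could be left to an analysis plan. The voiding rule and the three analysis sets are fixed in this document, so the point is not one of missing detail.

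**Conclusion.** The point holds as a weakness in a stated rule. An allocation that does not end in a transplant enters no efficacy or safety analysis set, the rule applies after the arm is known, and the exclusion can therefore depend on the arm.

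The size is unknown because no cancellation rate is given. Under the assumption of 3 to 5 losses per 133 counted as failures, power lies between 71% to 62% (all in HOPE) and 80% to 77% (equal in both arms), against 84% with none. A reader might take 62% as the expected cost. It is the extreme of that range and requires no losses at all in the control arm. If cancellations are rare or balanced, the effect is small, but the planned analyses could not show which case occurred.

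A reader might also infer that the two descriptions of randomization time cause more cancellations. The documents do not show this. They show only that the descriptions differ and that center practice decides. Randomization is stratified by center.

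**What to change.** 1. **Do not void allocations.** Keep the first allocation with its time and the reason for cancellation, stating whether the reason arose before or after the arm was known and before or after perfusion started. Report cancellations by arm and reason.
2. **Keep the full analysis set as primary, and add a sensitivity analysis** with one record per patient under the first allocation, so that a patient randomized twice is not counted twice. Count a graft discarded for a reason arising after allocation as a failure. This belongs in a sensitivity analysis only, because a graft never implanted has no early allograft dysfunction status.
3. **List arm-independent reasons in advance**, for example donor or recipient findings. Case-by-case judgement blind to arm is not workable, since a pump or cannulation reason reveals the arm.
4. **Include graft and device incidents between randomization and implantation in the safety tables**, even where no transplant follows.
5. **Reconcile the text** on three points: non-transplantable patients (Criteria for discontinuing {11b} against Sequence generation {16a}); the time of randomization (Table 1, footnote 2, against the inclusion visit and Sequence generation {16a}); and reporting before transplantation. On the last, the serious adverse event section covers organ conservation, while the section on events not requiring prompt notification limits collection during waiting-list time and the notification period opens at transplantation.

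The cost is a reason field, some added wording and a little more analysis, with a sensitivity estimate that may be slightly less favourable to HOPE. The audit trail already holds the cancelled randomizations, so much of this can be done for patients already enrolled. Changing the randomization time at every center would be a larger step: enrolment began in September 2019 and the expected conclusion is the end of February 2023.
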